#### 2.3.3. Phase 3: IPG Implantation

Subjects who succeed in the lead trial (at least 50% reduction of pain) will receive a PROCLAIM^TM^ System implant, depending on their electrical consumption (per following French ministry of health recommendations and implanting guidelines), and in view of preserving MRI compatibility, so as to be able to explore implanted patients with functional imaging during phase B.

In case of inadequate pain relief, impedance and lead position by radiographic imaging will be performed during the visits planned in the protocol or in supplementary visit. After ensuring that reprogramming cannot achieve pain relief and lead position by radiographic imaging, surgery could be performed to explore the failure to relieve pain by SCS or DRGS such as lead connection, defective lead or scar tissue formation.

To achieve SCS placement, the implanter should place the lead according to the cranio-caudal projection of the conus terminalis to anticipate/estimate a priori optimal lead placement.

### 2.4. Spinal Cord Stimulation Programming Modalities

Different waveforms will be used for the purpose of this study, including TCS and BurstDR^TM^. They differ in terms of amplitude, pulse width and frequencies. TCS delivers a constant stream of pulses:Pulse width: between 100 μs and 500 μs;Frequencies: between 30 Hz and 100 Hz;Amplitude: adapted to individual participant perception, the objective being to achieve a comfortable level of paresthesia. The minimum amplitude step size is 0.1 mA.

BurstDR^TM^ stimulation:40 Hz BurstDR^TM^ mode of constant-current stimuli with 5 spikes at 500 Hz per burst;Pulse width and interspike intervals of 1 ms;The minimum amplitude step size is 0.05 mA;Intermittent dosing: ratio from 1:3 (30-s ON and 90-s OFF) to 1:12 (30 s ON and 360 s OFF) [55].

The stimulation delivered by the IPG to the spinal or dorsal root ganglion target could depend on many parameters. First, it is well documented that CSF thickness varies according to the vertebral level and that the perception threshold is also impacted by the postural changes [56]. Positional effects have been attributed to a combination of factors including the distance between electrodes and the dorsal columns as well as the overall thickness of the CSF layer at the implanted spinal level [29]. These parameters clearly influence the current intensity delivered to the spinal cord [57] and consequently the paresthesia threshold generated by SCS [58]. On the other hand, DRGS is less likely to be impacted by these parameters due to a very thin layer of CSF surrounding the DRG. The distance between the lead and the neural target is quite small and presumably less sensitive to postural changes.

### 2.5. Clinical Assessments

Randomization is carried out at the IPG implantation visit. Subjects are assessed prior to randomization, during the inclusion visit and the lead implantation visit, and at 1-month, 2-month, 3-month, 4-month, 6-month and 12-month follow-up visits. Assessments are performed by appropriately trained and delegated study staff independently from industry. Details about which information will be collected at each visit can be found in Table 1.

#### 2.5.1. Primary Outcome

The primary outcome is the proportion of patients having a reduction of 50% on global VAS, assessed with a 5-day pain diary between baseline (before lead implantation) and after each period of the crossover phase. Patients record their global, back and leg pain using a pain diary once a day, for a 5-day period within one week prior to each scheduled study visit.

#### 2.5.2. Secondary Outcomes

Secondary outcomes that will be compared between treatments and waveforms are changed between baseline and each follow-up visit in each of the following scores: pain intensity (VAS), pain surface (in cm^2^), percentage of pain covered with paresthesia and lead selectivity (percentage of paresthesia covering pain); paresthesia discomfort measured by an 11-point numeric rating scale (NRS) while sitting, standing and lying down; health-related quality of life measured by the EuroQol 5 Dimensions 5 Level (EQ-5D-5L) questionnaire; functional disability measured by the Oswestry Disability Index (ODI); anxiety and depression symptoms measured by the Hospital Anxiety and Depression Scale (HADS) and the Pain Catastrophizing Scale (PCS); and patient satisfaction measured by the Patient Global Impression of Change Scale (PGIC). Safety will be evaluated by adverse events (AE), serious adverse events (SAE) and device deficiencies from inclusion to 12-month follow-up.

Only for patients enrolled at Poitiers University Hospital: the effects of stimulation modalities on brain imaging will be measured by MRI Blood Oxygen Level-Dependent (BOLD) signal and Fractional Anisotropy (FA) resting state condition (stimulation switch off). Effects of stimulation on brain electrical activity will be measured by EEG signal of the posterior cingulate cortex (PCC), the pregenual anterior cingulate cortex (pgACC) and ventromedial prefrontal cortex (vmPFC), pgACC/vmPFC with stimulation switched on.

We will also evaluate stimulation efficacy using a published and clinically validated composite factor that allows for the multidimensional evaluation of patients [59]. Patients having at least three of the criteria listed below will be considered as good responders:Regaining functional capacity: having at least a 30% decrease in Oswestry Disability Index (ODI) percentage.Adequate global pain relief: having at least a 50% decrease in the Visual Analogic Scale (VAS).Improvement in quality of life: having at least a 0.2 increase in the EuroQol-5 Dimensions (EQ-5D) questionnaire.Decrease in psychological distress: having a decrease of at least 1.4 points in the Hospital Anxiety and Depression Scale (HADS) depression score.Decrease of at least 30% in pain surface (percentage of cm^2^): pain surface and its properties will be assessed using a pain mapping tool.Having a Patient Global Impression of Change (PGIC) score of at least 6/7.Drug intake: drug intake will be measured using the Medication Quantification Scale (MQS) and a reduction of at least 3.4 points will be considered as meaningful.

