First, pauci-discriminative stimulation of billions of sensory epicritic fibers of the dorsal columns using electrical impulses makes it very complex for SCS to be selective in terms of pain coverage for patients [11]. This lack of selectivity, associated with the type of implanted lead, its positioning, its properties, patient variability and the challenge to provide adequate spatial and temporal neural targeting using electrical source-specific capabilities, can lead, on the one hand, to feel paresthesia in a non-painful area and, on the other hand, to not be able to cover decisive painful body regions and/or pain trigger(s), particularly in focal distal pain distribution, as in foot and groin pain [12]. As described by Holsheimer et al. [13], lead positioning can dramatically impact paresthesia coverage and energy consumption. New available paresthesia-free waveforms, such as burst, high frequency or high dose, appear to limit this problem by suppressing patient perception of the therapy [14,15,16,17,18,19]. However, they might also result in significantly higher energy consumption, requiring more frequent recharges, or lead to premature battery replacement. Third, a decrease/loss of effectiveness may occur over time [8] due to neural plasticity. This might explain why, up until now, physicians have been obsessively focusing on pain coverage, expending considerable energy to blur nociceptive signals by stimulating long sensory fibers with various SCS spatial programming strategies [4], rather than attempting to stimulate other potential pain generators. One major target appears to be located at the dorsal root ganglion (DRG) level and plays a crucial role in pain generation [20,21]. To validate this hypothesis, medical device and neuromodulation industries have developed DRG stimulation (DRGS) [22]. DRGS appears to be a promising technology for patients suffering from refractory chronic neuropathic pain, and particularly focal pain, since it operates more selectively on the nervous system [22,23,24,25,26,27,28]. Furthermore, DRGS could have an advantage over SCS by processing less positional sensitivity, possessing more stability and superior electrical efficiency in terms of energy consumption. Due to its proximity and lack of cerebro-spinal fluid (CSF), it requires far less amplitude to deliver therapy to the appropriate neural target [13,29]. In a recent high-quality prospective, multicenter, randomized comparative trial conducted on 152 subjects implanted with either an SCS or a DRG stimulation system, Deer et al. [24] reported that DRGS leads to a significantly higher rate of treatment success (≥50% pain relief) compared with conventional SCS (81.2% vs. 56.7%, respectively) in patients with complex regional pain syndrome (CRPS) and/or causalgia. The authors also reported that, using DRGS, pain relief was maintained through 12 months of follow-up and was greater than with SCS. However, in this study, SCS and DRGS were assessed in two distinct groups of CRPS patients, between whom comparison was not possible. Some might not have responded to SCS or DRGS due to their baseline latent confounding variables rather than therapy efficacy variability. Furthermore, synergy between SCS and DRGS working simultaneously on the same patient might catalyze therapy outcome by optimizing spatial and temporal neural tissue targeting, pain coverage (i.e., selectivity), pain relief, cortical perception and, ultimately, electrical consumption. This has never been documented so far.

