### Aims and Objectives

The BOOST DRG study is a randomized, controlled trial comparing the efficacy of SCS vs. DRGS vs. combination of SCS+DRGS (DUAL) and TCS vs. burst in a crossover design in patients with chronic lower limb neuropathic pain and/or neuropathic back pain.

The primary objective of this study is to compare the efficacy of SCS vs. DRGS vs. DUAL on global pain relief in patients with chronic lower limb neuropathic pain and/or neuropathic back pain.

Secondary objectives are to compare pain intensity, pain surface and paresthesia coverage surface to assess positional or postural effects on paresthesia, to compare changes in quality of life, functional disability and psychological state, to assess patient satisfaction and, finally, to compare the effects of stimulation modalities on brain imaging based on fMRI and EEG. Using this study data, we will extract baseline factors associated with long-term stimulation efficacy. These predictors will be included in a predictive model.

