#### 2.7.2. Main Statistical Analysis

Statistical analysis will be conducted using R software (Version 3.1.2, R Foundation for Statistical Computing, Vienna, Austria).

Data from phase A (12 patients) and phase B (54 patients) will be pooled (66 patients) for the main analysis.

Normality of distributions will be tested using the Shapiro–Wilk test. Either parametric or non-parametric methods will be used depending on the normality test results.

Our primary objective is to compare the efficacy of SCS, DRGS and DUAL stimulation at the crossover period based on the “50% VAS decrease” outcome.

Since our primary endpoint is a binary variable, we will use a mixed-effects logistic regression model, where the fixed effects are as follows: the treatment effect, the period effect and their interaction. The random effect is the random subject intercept. Fixed effects, their 95% confidence intervals and their significant level will be reported. Models will be estimated using restricted maximum likelihood estimation using the lmer function from the lmerTest package.

In case of significant effect of period and treatment, a two-step procedure will be conducted to assess pairwise differences between treatment effects. First, treatment effects will be estimated using a mixed-effects model as previously described, using data from each pair of treatments. Next, we will apply Holm–Bonferroni method to keep family-wise error under the 0.05 significance level.

In case the period effect is not significant, a Cochran Q test will be used to test the differences between the three groups. If the null hypothesis of the Cochran Q test is rejected, a McNemar test will be conducted for pairwise comparisons of the three groups. A Holm–Bonferroni correction will be applied to the *p*-values following the pairwise comparisons.

For the secondary outcomes, a two-factor repeated measure ANOVA (treatment + period factors) will be used to compare the continuous outcomes between the three treatments and a mixed effect logistic/multinomial regression model will be used to compare the categorical outcomes similarly to the analysis of the primary outcome. If the omnibus test’s *p*-value is significant, a pairwise comparison procedure with Holm–Bonferroni correction will be conducted.

At the 4-month period, the proportions of patients preferring the DRGS, the conventional SCS or the DUAL stimulation will be compared using a Chi-squared test.

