Continuous outcomes at 4-month of burst DRGS, burst SCS and burst DUAL stimulations will be compared using an ANOVA or a Kruskal–Wallis test. In case the ANOVA (or Kruskal–Wallis test) is significant, a pairwise comparison will then be conducted using independent *t*-test or Mann–Whitney test depending on the variable distribution. A Holm–Bonferroni correction will be applied on the pairwise comparison.

The categorical outcomes will be compared using a Chi-squared test or an exact Fisher test when the Chi-squared assumptions are not met. A generalized mixed-effects model with a patient specific random intercept will be used to estimate the global treatment effect including the 6-month and 12-month follow-ups. The link function used in the model will depend on the type of the studied outcome (logistic or multinomial for categorical outcomes and no link function for continuous outcome).

The relationship between performance (percentage of pain covered with stimulation) and “induced” pain relief (global pain VAS) will be estimated by Kendall’s tau and its 95% confidence interval. The correlation between selectivity (percentage of paresthesia covering pain) and paresthesia discomfort will also be estimated using Kendall’s tau.

Mean energy consumption will be compared between the different types of stimulation using repeated measures ANOVA or a Friedman test.

Tonic stimulation will be compared to burst stimulation using patient last crossover stimulation modality. The comparison will be conducted using a paired *t*-test or a Wilcoxon signed-rank test using data from the last crossover period compared to the 4-month data using burst stimulation. VAS decrease will be compared between all the SCS modalities at 6-month and 12-month follow-ups using a two-factor ANOVA (preferred anatomical target x preferred stimulation type).

A sub-analysis of the sample will be conducted in order to assess the effect of burst waveform on the brain signals visualized using brain imaging data with and without burst stimulation.

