Two interim analyses are planned. The first interim analysis will be conducted on data from the first 12 patients included (after the “Tonic” crossover period). In this first interim analysis, we will analyze only the safety criteria, the objective being to assess study feasibility. The second interim analysis will be conducted on data from the first 33 patients included (after the “Tonic” crossover period) and will be exclusively descriptive. No hypothesis testing will be conducted. This analysis will be conducted on primary and secondary outcomes. As the study is of long duration (3.5 years), we decided to include a second interim analysis to communicate the results to the scientific community by clearly indicating that this is an interim analysis and that the final analysis will be conducted on the total sample of 66 patients. This may lead to other projects and accelerate the progress of research on the stimulation of several anatomical targets. These results will have no impact on study completion. The final analysis on 66 patients will be considered for the report and the publications.

Only data from the crossover period will be used in the interim analysis. The statistical methods used in this interim analysis will be similar to the methods used in final analysis described above. No adjustment of the final analysis *p*-values will be conducted as the interim analysis results do not influence in any way the course or the conduct of the study.

A significance level of 0.05 will be considered in this study (after taking into account multiple testing corrections) and all tests will be two-sided.

All the analyses will be conducted based on an Intention-To-Treat (ITT) principle using complete cases. No missing data imputation will be conducted. An initial safety analysis will be conducted on the first 12 patients to assess the initial safety of implementing patients with both DRG and SCS stimulations. A final safety analysis will be conducted on the 66 patients. Frequencies of adverse events and deviations from protocol will be compared between the treatments following an ITT analysis.

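### The treatment + period ANOVA fixed for paresthesia discomfort compares its level between modalities, so the secondary objective on positional effects has no analysis that tests change with posture

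*Protocol article*

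**What the plan says.** Aims and Objectives lists among the secondary objectives "to assess positional or postural effects on paresthesia". The expected direction is given as background. The Introduction says "DRGS could have an advantage over SCS by processing less positional sensitivity", and section 2.4 describes the DRG target as "presumably less sensitive to postural changes".

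Section 2.5.2 names the outcome, "paresthesia discomfort measured by an 11-point numeric rating scale (NRS) while sitting, standing and lying down", and Table 1 schedules it at every visit from M1 to M12. The same section states the comparison: "Secondary outcomes that will be compared between treatments and waveforms are changed between baseline and each follow-up visit".

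For the crossover period, section 2.7.2 fixes the model: "a two-factor repeated measure ANOVA (treatment + period factors) will be used to compare the continuous outcomes between the three treatments". The same section names discomfort once more, in a Kendall's tau: "The correlation between selectivity (percentage of paresthesia covering pain) and paresthesia discomfort". Its remaining analyses are a comparison of the burst groups at 4 months, a paired tonic-versus-burst test and a mixed model over the 6- and 12-month visits. None of them names posture as a factor, a posture interaction, a between-posture difference, or a way of combining the three ratings.

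**The concern.** A positional effect is a difference between postures in the same patient under the same modality. The expectation that DRGS is less sensitive than SCS is then a question about treatment by posture. A treatment + period model asks something else: whether mean discomfort differs between SCS, DRGS and DUAL. A modality can score higher in every posture and be perfectly stable, or have the same average as another and swing widely.

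Two wrong readings are possible. If the ratings are averaged, a real difference in stability can be reported as no difference. If they are analysed one posture at a time, a plain difference in discomfort can be read as a positional advantage. With no stated choice between average, single postures and differences, the choice could also be made after the data are seen.

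**Working it through.** The protocol gives no figure for this analysis, so there is nothing to reproduce. The check is structural, with an illustration.

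**Structure.** Let μ(t,k) be mean discomfort under modality t in posture k. The stated ANOVA, run on one posture, tests whether μ(t,k) is equal across t for that k. Run on the average, it tests whether the mean over k is equal across t. The objective concerns μ(t,k) − μ(t,k′), and whether this difference depends on t. Neither version of the stated test addresses that.

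**Illustration 1: n = 48 (section 2.7.1), six sequences, three periods, two-sided 0.05.** Assumed, not in the documents: patient-by-period SD 1.0 and residual SD 1.2 NRS points (between-patient SD 1.5, which cancels). The F test has 2 and 144 − 48 − 4 = 92 degrees of freedom. Its noncentrality is λ = n Σ(δt − δ̄)²/σ², where δt is the effect of modality t. The variances are:
- one posture: 1.0² + 1.2² = 2.44
- mean of three postures: 1.0 + 1.44/3 = 1.48
- lying minus the mean of sitting and standing: 1.44 × 1.5 = 2.16

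Scenario A has equal average discomfort. Deviations for sitting/standing/lying are SCS −0.5/−0.5/+1.0, DUAL half of that, and DRGS zero. Scenario B has no posture effect, with DRGS 1 point and DUAL 0.5 point below SCS in every posture.

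| Test | Scenario | Σ(δt − δ̄)² | λ | Power by formula | Simulated (4,000 runs) |
|---|---|---|---|---|---|
| Posture mean | A | 0 | 0 | 5% | 5.4% |
| Sitting, standing | A | 0.125 | 2.46 | 26% | 26%, 27% |
| Lying | A | 0.5 | 9.84 | 80% | 78% |
| Posture contrast by modality | A | 1.125 | 25.0 | over 99% | 99% |
| Posture mean | B | 0.5 | 16.2 | 95% | 95% |
| Each posture | B | 0.5 | 9.84 | 80% | 80% |
| Posture contrast by modality | B | 0 | 0 | 5% | 4.3% |

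In a third scenario all modalities vary equally with posture. Every treatment + period ANOVA then stays at 4 to 5%, so a posture effect common to all three is not seen either.

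**Illustration 2: n = 55 (66 × 0.83 = 54.8), scores rounded and bounded at 0 to 10.** Assumed: patient SD 1.5, residual SD 1.5; 1,500 runs per scenario.
- Systematic gradient (sitting/standing/lying: SCS 2/3/4, DRGS 3/3/3, DUAL 2.5/3/3.5): the posture mean rejects in about 5 to 7%, the per-posture tests in about 84%, 4% and 86%, and the posture contrast by modality in about 96%.
- Level only (DRGS 1 and DUAL 0.5 below SCS, no posture effect): the per-posture tests reject in about 85% each and the contrast in about 4 to 7%.
- Within-visit range (maximum minus minimum) with no posture effect: it rejects in about 12% at levels 3/2/2.5 (SCS/DRGS/DUAL) and in 62 to 65% at levels 3/1/2. Scores near zero are compressed, so the range follows the level.

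**The case against.** The strongest reply is that this is a condensed article. One general sentence covers all continuous secondary outcomes, and how three posture ratings are handled is often left to the analysis plan, which is not shown and may contain the term. That limits the point to what the article fixes, but does not remove it. The article states a model with two named factors. It gives tailored analyses for other secondary questions, one of which involves discomfort itself, and still has none for posture.

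Second, one ANOVA per posture is a natural reading of section 2.5.2, and under a systematic gradient it would react in two of three postures. This stands: the stated plan is not blind to such a pattern. Those tests still cannot separate a posture effect from a uniform difference in level.

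Third, the lower sensitivity of DRGS is worded tentatively and as background; the objective itself gives no direction. This also stands. Assessing a postural effect still requires a comparison between postures, whatever direction is expected.

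A reader might infer that the objective cannot be answered by this trial. The documents do not support that: all three ratings are planned in the same patient at each visit from M1.

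A reader might also think of patients who each have a different worst posture. All mean-based tests, including the interaction, could miss that pattern. Nothing in the documents indicates it, and the mechanism in section 2.4 (electrode distance and CSF thickness) points rather to a systematic effect.

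**Conclusion.** The mismatch is real and confined to one secondary objective. The stated model tests the level of discomfort, whereas the objective concerns change with posture. That follows from the factors named and depends on no assumed value.

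The percentages do depend on the assumed SDs and effects. Under them, averaging over postures leaves rejection at about chance when only posture sensitivity differs. Per-posture tests give nearly the same rejection rate for a true gradient (about 84% and 86% in two postures) as for a pure level difference (about 85%). A posture contrast by modality separates the two cases (about 96% against about 5%).

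The conclusion is that the stated analysis does not answer the objective, not that the data cannot. An analysis plan that is not shown may already close the gap.

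**What to change.** In section 2.7.2, state for paresthesia discomfort that the three NRS values at each crossover visit enter one repeated-measures model. Its factors are treatment, period, posture and treatment x posture, and it should allow for correlation within patient and within visit. Use the treatment x posture test, or between-posture contrasts by modality, for the positional objective, with Holm correction of the pairwise comparisons. The posture main effect then covers a change common to all modalities.

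Keep the comparison of level as a separate discomfort outcome. Report the within-visit range descriptively only, because on a bounded scale it depends on the level.

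The change is wording: no new data, visits or patients. Its cost is one additional secondary test.
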